### Sample size

#### Registry set

According to the relevant literature and data, the average morbidity rate of neural function deterioration is 38.6% [9–11, 34, 35]. The aim of the hybrid operation is to reduce the rate of neural function deterioration by 10%, referring to present studies [31–33]. To ensure the statistical power and the potency of exploring technical details, the sample size is set as the maximum operative capacity of participating centers. According to the records of the latest 5 years, the operative capacity of Beijing Tiantan Hospital is about 220 cases of bAVMs per year, and of other participating centers is 20 cases per year in total. A total of 1200 cases will be recruited into the cohort in the 5-year-recruitment. Among them, 800 cases will receive hybrid operations, and 400 cases will receive microsurgical operations.

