### Outcome evaluation

The primary outcome is defined as neural function deterioration (an increased mRS and mRS > 2) in the 3 months after operation. The neural function will be evaluated 48 h and 7 days after operation while hospitalized and at 3 months, 6 months and 12 months after discharge. A deterioration will be considered temporary if it is sustained < 12 months, otherwise it will be considered permanent. The secondary outcomes will include the postoperative mortality, operation-related complications, and bAVMs residue. The postoperative mortality will include death that occurs within 7 days from the date of operation. Operation-related complications will include any complications that occur within 7 days from the date of operation, including intracranial hemorrhage or infarction, infection of the central nervous system, infection of the respiratory system, cranial nerve deficits, and other symptomatic complications. The bAVMs residue will be diagnosed on the basis of DSA or CTA after operation. The mRS fluctuation will also be recorded and defined as the consecutive changing value of mRS between different follow-up points. The evaluations and diagnoses will be conducted by the physicians who have not learnt about the patients and collected by CRCs.

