### Data management

All the data in this study will be sourced from experienced physicians and radiologists in 20 participating centers, and they will be prospectively collected by full-time clinical research coordinators (CRCs) using both paper documents and a web-based electronic data capture system (EDC system). SUN HEALTH (Beijing) Health Care Group, a third-party CRO, is contracted to render the services of quality control and data management. The study is supervised and administered by the Ministry of Science and Technology of China and the Beijing Municipal Science and Technology Commission, and it receives resource support from the China National Clinical Research Center for Neurological Diseases. Issues that occur in the cohort will be reported to oversight authorities and evaluated. All data are available only to participating centers while the study is being conducted and will become public once the study concludes. All of the processes of data collection, statistical analysis, study result interpretations and dissemination are under the direct supervision of the principal investigator. The final results will be disseminated via printed media in December 2020.

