### Duration of study

The study was approved and authorized to launch in September 2016 and was specified to close in December 2020. The recruitment of participants began on 1st January 2016 in the pilot study that had been launched. Participants enrolled after 1st September 2016 were involved in this study.

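### The registry total of 1200 needs 60 months of recruitment, but one section allows only 52, and closing and reporting in December 2020 leaves no follow-up for the last patients

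*Protocol article*

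**What the plan says.** All references are to the protocol article.

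- **Sample size, Registry set.** The size is not derived from a power calculation: "the sample size is set as the maximum operative capacity of participating centers". For the host hospital, "the operative capacity of Beijing Tiantan Hospital is about 220 cases of bAVMs per year"; the capacity "of other participating centers is 20 cases per year in total". Then: "A total of 1200 cases will be recruited into the cohort in the 5-year-recruitment", of whom "800 cases will receive hybrid operations, and 400 cases will receive microsurgical operations".
- **Abstract (Methods) and Study design.** Both give January 2016 to December 2020 as the period in which the study is conducted.
- **Duration of study.** Approval and launch are dated September 2016 and closure December 2020. Recruitment from 1 January 2016 is attributed to a pilot study, and "Participants enrolled after 1st September 2016 were involved in this study".
- **Data management.** "The final results will be disseminated via printed media in December 2020".
- **Outcome evaluation.** The primary outcome is neural function deterioration in the 3 months after operation. Later visits are at 3, 6 and 12 months after discharge. "A deterioration will be considered temporary if it is sustained < 12 months, otherwise it will be considered permanent".

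**The concern.** Two things do not fit together.

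First, the total uses the whole of January 2016 to December 2020 at full capacity, with nothing in reserve. If the Duration of study section governs, eight of those 60 months belong to the pilot and their patients are not part of this study.

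Second, recruitment, follow-up, closure and publication all end in the same month. A patient operated on in the last quarter of 2020 cannot have a 3-month outcome by then, and a patient operated on at any time in 2020 cannot have a 12-month visit. The second problem does not depend on the first, because it remains if the pilot patients are counted.

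At stake are the registry's stated size and its 800/400 split, the completeness of the primary outcome, and the ability to separate temporary from permanent deterioration in the last year's patients.

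**Working it through.** **Inputs.** Capacity 220 + 20 = 240 cases a year, or 20 a month (Sample size, Registry set). Start January 2016 (Abstract, Study design) or September 2016 (Duration of study). Close and report December 2020 (Duration of study, Data management). Outcome times 3 and 12 months (Outcome evaluation).

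**The plan's own figure.** 240 × 5 = 1200. It is reproduced exactly, so the arithmetic is right for a 60-month window.

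**With the September 2016 start.** September 2016 to December 2020 is 4 + 48 = 52 months. 52 × 20 = 1040, which is 160 (13%) below 1200. Reaching 1200 in 52 months would need 1200 ÷ 52 × 12 ≈ 277 cases a year, about 15% above the stated maximum of 240.

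**Patients who could complete follow-up by 31 December 2020, at 20 a month:**

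| | September 2016 start | January 2016 start (pilot counted) |
|---|---|---|
| Operated on by end of December 2020 | 52 × 20 = 1040 | 60 × 20 = 1200 |
| 3-month outcome possible | 49 × 20 = 980 | 57 × 20 = 1140 |
| 12-month visit possible | 40 × 20 = 800 | 48 × 20 = 960 |

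Under either start, if recruitment runs to the end, 3 × 20 = 60 patients lack the 3-month outcome and 12 × 20 = 240 lack the 12-month visit.

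These are ceilings. They assume that every operated lesion is eligible and every patient consents. They time follow-up from operation, although the later visits run from discharge, and they allow no time for data cleaning or publication.

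**Effect on power for the 3-month outcome.** The registry section states neither a power nor an alpha, and does not say whether its 10% reduction is absolute or relative. Assume two-sided alpha 0.05, 2:1 allocation and an absolute reduction from p₁ = 0.386 (traditional, n₁ = N/3) to p₂ = 0.286 (hybrid, n₂ = 2N/3):

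power = Φ[(|p₁ − p₂| − 1.96·SE₀) / SE₁]

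where SE₀ = √[p̄(1 − p̄)(1/n₁ + 1/n₂)], SE₁ = √[p₁(1 − p₁)/n₁ + p₂(1 − p₂)/n₂] and p̄ = (0.386 + 2 × 0.286)/3 = 0.319.

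| N | SE₀ | SE₁ | Power |
|---|---|---|---|
| 1200 | 0.0285 | 0.0291 | 0.93 |
| 1040 | 0.0307 | 0.0313 | 0.90 |
| 980 | 0.0316 | 0.0322 | 0.88 |

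If 10% is relative (38.6% against 34.7%), the same formula gives 0.26, 0.23 and 0.22. On either reading the shortfall itself moves power by about five points or less.

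**The case against.** The strongest reply is that the sample size section contains no arithmetic error. Five years at 240 a year is 1200, and the Abstract and Study design section give the same five-year window. Only the Duration of study section departs from it. If the pilot patients count, 1200 can be recruited. This stands: a reader might infer that 1200 is flatly unattainable, but that holds only under the September 2016 start and at the stated capacity. The defect is a conflict of dates that the sponsor must resolve. The reply does not rescue follow-up, because even with the pilot counted no more than 1140 patients could have the primary outcome and 960 the 12-month visit.

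A second reply is that little power is lost. This also stands. The registry claims no power, so none is breached. A reader might take power at 800, the number with a 12-month visit, but the primary outcome is at 3 months, so 980 is the relevant count.

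Third, a reader might infer that late patients' deteriorations will be labelled temporary by default, so that permanent harm is systematically under-counted. The article does not support this. It classifies by how long a deterioration is sustained and does not say how truncated observation is handled, which the full protocol or analysis plan may settle. It also gives no rate of persistence, so no number of misclassified patients can be derived. Temporary versus permanent status is not among the listed primary or secondary outcomes either. What remains is narrower: about 240 patients would lack the visit on which that distinction depends.

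**Conclusion.** The point holds as an inconsistency between the stated registry total and the stated dates, together with a follow-up gap that exists whichever start date is right.

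- With the September 2016 start, at most about 1040 cases can be recruited at stated capacity, not 1200.
- With closure and reporting in December 2020, the ceilings are about 980 patients with the primary outcome and 800 with the 12-month visit (1140 and 960 if pilot patients count).
- If recruitment continues to the end, about 60 patients lack the primary outcome. That is 60/1040, about 6%, or 60/1200 = 5% with the pilot counted. About 240 lack the 12-month visit.

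The main harm is a total that may not be deliverable and incomplete outcomes, not loss of power. The counts assume even accrual at 20 a month; the host hospital's capacity is itself given only approximately. The power figures rest on the assumed alpha and the absolute reading of the 10% reduction. The randomised trial set's 236 patients are sized separately, and their number is not affected by the 1200 calculation.

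**What to change.** 1. Reconcile the dates in the Abstract, Study design, Sample size (Registry set), Data management and Duration of study sections, and state whether patients recruited from January to August 2016 count.
2. If they do not count, restate the registry target as at most about 1040 and scale the 2:1 split to match: 1040 × 2/3 ≈ 693 hybrid and 1040 × 1/3 ≈ 347 traditional.
3. In either case, set a last-operation date, or move data lock and reporting, so that every analysed patient can complete the 3-month and 12-month assessments. State the numbers expected at each.
4. Report patients without a 12-month visit as unclassified for temporary or permanent status.

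The cost is a few restated figures and dates, one sentence on classification, and either an earlier end to enrolment or a later report. At 20 cases a month, stopping operations at the end of December 2019 to keep the December 2020 date gives up about 240 patients. Keeping enrolment open to December 2020 instead delays lock and reporting by at least 12 months.

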#### Trial set

Few studies have been found on bAVMs with perforating feeding arteries. Referring to relevant studies of bAVMs, the neural function deterioration rate was 38.6% in traditional operation and 19% in one-staged hybrid operation. By using PASS 14 (PASS Power Analysis and Sample Size software, NCSS, LLC, Utah, US) with a significance level of 0.05 and a statistical power of 0.9, the minimum sample size for each group is *n* = 117. In total, 236 patients will be enrolled in the trial set.

### Statistical analyses

Statistical analyses will be conducted using the Statistical Package for the Social Sciences software (V.22.0; SPSS, Chicago, Illinois, USA). Demographic information (age, gender, race, provenance, occupation), medical histories (primary symptom, operation history, and past history, family history, smoking and drinking history), bAVM-related morphological and location features (eloquences and fiber tracks involved according to the task), angioarchitectural features (origin and type of feeding arteries, situation of nidus and draining veins), and admitting conditions (signs, mRS score and NIHSS score) will be cataloged into continuous or categorical variables and descriptively analyzed. The baseline conditions of cases involved in the two groups will be compared by the characteristics described above. The Chi-square test and Student t-test will be conducted between homogeneous cases of 2 groups in the outcome variables, including operation-related events (e.g., operative time, hemorrhagic volume, electrophysiological changes) and outcomes to make comparisons of their safety and efficiency in several aspects. Univariate and multivariate logistic regression analyses will be conducted to explore the correlations between the outcome index and variables above. Analyses of subgroups in the hybrid operation group will be performed to evaluate the contributions of different endovascular interventions. In the trial set, differences will be tested with Chi-square test. The effect of hybrid operation in the subgroup will be clarified.

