All patients involved are introduced to the operative process, advantages and shortcomings of one-staged operation and traditional operation. Individualized risks of the two methods are evaluated in the preoperative discussion and announced to the patients. Participants make the selection after weighing the benefits, risks and financial burden of different operative methods. As the majority of medical expenses are covered by the Urban Residents’ Basic Medical Insurance and Rural Cooperative Medical Service for Chinese citizens, there is no extra financial compensation in this study.

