### Group assignment and treatment

In the registry set, patients will be assigned to the TO group or the HO group on the basis of clinical conditions and personal wishes. Patients in the HO group will receive microsurgical operation under the assistance of endovascular embolization or balloon occlusion. Patients in the TO group will receive only traditional microsurgical operations, and a repeated DSA will be arranged 3 days after the operation.

In the trial set, patients who refuse the randomized group assignment will be enrolled in the registry set. Those who agree will be randomly (by central randomization system) assigned to the TO group or the HO group. The interventions of each group will be the same in the two sets.

The functional MRI-based neuro-navigation and intraoperative Doppler ultrasound will be used as essential assistance in all operations.

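### The registry compares self-selected groups with crude tests on undefined homogeneous cases, and no adjusted effect of operation group is named as the comparison

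*Protocol article*

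**What the plan says.** All references are to the protocol article.

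- **Assignment** (Group assignment and treatment): the rule given for the registry is that "patients will be assigned to the TO group or the HO group on the basis of clinical conditions and personal wishes". Patient and public involvement adds that "Individualized risks of the two methods are evaluated in the preoperative discussion and announced to the patients" and that "Participants make the selection after weighing the benefits, risks and financial burden of different operative methods".
- **Group comparison** (Statistical analyses): "The Chi-square test and Student t-test will be conducted between homogeneous cases of 2 groups in the outcome variables". The stated purpose of these tests is to compare the safety and efficiency of the two operations.
- **Baseline** (Statistical analyses): "The baseline conditions of cases involved in the two groups will be compared by the characteristics described above". No consequence for the outcome analysis is attached.
- **Regression** (Statistical analyses): "Univariate and multivariate logistic regression analyses will be conducted to explore the correlations between the outcome index and variables above". The variables listed earlier in that section are demographics, history, lesion features, angioarchitecture and admission status. Operation group is not named as a term.
- **Target** (Sample size, Registry set): "the average morbidity rate of neural function deterioration is 38.6" per cent, and "The aim of the hybrid operation is to reduce the rate of neural function deterioration by 10" per cent. The plan is 1200 cases, 800 hybrid and 400 microsurgical.
- **Overlap with the trial set** (Study design): the registry covers the whole data pool, so trial-set patients are in it too. The trial set plans 236 patients.

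**The concern.** When lesion features and an individual risk estimate help to decide the operation, the two groups can differ in prognosis before surgery. A chi-square test or t-test then mixes the effect of the operation with the effect of case mix. Restricting the test to comparable cases could deal with this, but only if comparable is defined. As written, a reader cannot tell which confounders the restriction controls, how many of the 1200 patients remain, or whether the choice is made without sight of outcomes.

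The article says that safety and efficiency will be validated in the registry. If the crude tests carry that conclusion, it could reflect who was selected for hybrid operation and not what the operation does. The large sample does not help: it shrinks random error and leaves the bias unchanged.

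**Working it through.** **1. The plan's own figure.** Registry size: (220 + 20) cases per year × 5 years = 1200, split 800/400. This reproduces exactly. No power is stated for the registry.

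**2. Random error at that size.** Assume a two-sided 0.05 test; the article gives 0.05 for the trial set only and does not state sidedness. With d the difference in rates, SE0 the pooled and SE1 the unpooled standard error, the rejection probability is Φ((|d| − 1.96·SE0)/SE1), with 400 against 800.
- 10% read as absolute, 38.6% against 28.6%: power 0.935. The pooled rate is (400×0.386 + 800×0.286)/1200 = 0.319, so the smallest significant crude difference is 1.96·√[0.319×0.681×(1/400 + 1/800)] ≈ 5.6 points.
- 10% read as relative, 38.6% × 0.9 = 34.7%: power 0.26.

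On the absolute reading random error is small, so systematic imbalance is the main threat.

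**3. Illustration of bias with no true effect.** The stratum risks and imbalances below are assumptions; the article gives none. Easier lesions deteriorate in 20%, harder in 50%. With share q of harder lesions, the group rate is 0.2(1 − q) + 0.5q, so the crude difference is 0.30 × (difference in q). No restriction to homogeneous cases is applied.

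| Share of harder lesions, TO / HO | Patients | Rates, TO / HO | Spurious difference | P(reject) |
|---|---|---|---|---|
| 60% / 40% | all 1200 self-selected | 38.0% / 32.0% | 6.0 points | 0.54 |
| 60% / 40% | 236 of the 1200 randomised | 37.1% / 32.4% | 4.7 points | 0.36 |
| 70% / 30% | all 1200 self-selected | 41.0% / 29.0% | 12.0 points | 0.98 |
| 70% / 30% | 236 of the 1200 randomised | 39.2% / 29.9% | 9.3 points | 0.90 |

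First row: pooled rate 0.34, SE0 = √(0.34×0.66×0.00375) = 0.0290, SE1 = 0.0293, so Φ((0.060 − 0.0569)/0.0293) = 0.54.

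In the rows with 236 randomised, 118 per arm have 50% harder lesions and hence a rate of 35%. For the second row:
- TO: (118×0.35 + 282×0.38)/400 = 0.371
- HO: (118×0.35 + 682×0.32)/800 = 0.324

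A 10-point imbalance with all 1200 self-selected gives 0.30 × 0.10 = 3 points and rejection probability about 0.18.

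**4. The opposite direction.** If hybrid patients had the harder lesions, the same arithmetic would hide benefit. A true 10-point reduction in each stratum with a 20-point imbalance shows as 10 − 6 = 4 points.

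**5. Does the planned regression close the gap?** Side by side, the Statistical analyses section ties the comparison of operations to the crude tests and ties the regression to exploring correlations with the listed baseline variables. Nothing makes a regression coefficient for operation group the treatment comparison.

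**The case against.** The other side has real weight.

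- **The illustration is not the planned analysis.** The tests are limited to homogeneous cases. If that means similar lesion difficulty, most of the assumed imbalance disappears. This stands: the figures apply only without an effective restriction.
- **Not every registry patient is self-selected.** Up to 236 may be randomised, which lowers the illustrated bias to 4.7 and 9.3 points. This stands too.
- **Adjustment is not absent.** Multivariable regression is planned, and reading its exploratory wording as excluding a group effect is interpretation. This stands in part. Nobody should say that the plan has no multivariable analysis, but the text does not give that model the comparative role.
- **Matching criteria and covariate lists belong in a fuller document.** True of the lists. The point here is narrower: the article itself names the tests and the population for the comparison, and what it fixes leaves confounding open.
- **Selection is not by prognosis alone.** Personal wishes and financial burden also count. This stands, though it does not make the groups comparable.

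A reader might infer more: that small prognostic differences will be declared significant, or that bias exceeds a 10-point target. The documents support neither. The 3-point example rejects only about 18% of the time, no confounding size or direction is given, and the article does not say whether 10% is absolute or relative. Nor does it say that cases will be chosen after outcomes are seen; it merely does not rule this out.

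**Conclusion.** The point holds as a fault in what the article fixes for the registry: treatment is chosen, the named comparison is crude tests on an undefined subset, and the planned regression is not assigned to estimate the effect of operation group. The randomised comparison in the trial set is unaffected.

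The size of the bias cannot be derived from the documents. Under assumed risks of 20% and 50% and a 20-point imbalance it would be 6 points, or about 4.7 with 236 balanced randomised patients included. These figures show only that bias could matter beside a target of 10 points (absolute reading) or 3.9 points (relative reading, 38.6 − 34.7). They are not a forecast.

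**What to change.** 1. Name one prespecified, confounder-adjusted effect of operation group, with 95% CI, as the registry's main comparison in the non-randomised patients. The simplest route is the multivariable logistic regression already planned, with operation group included and the result standardised to a risk difference. Choose one method, since alternatives such as overlap weighting target a different population.
2. Fix the covariates in advance from baseline data that the article describes: Spetzler-Martin grade, eloquence, feeder type, haemorrhagic presentation, admission mRS, age, operation history and centre.
3. Either define homogeneous cases by baseline variables set before outcomes are seen, or drop the restriction.
4. Keep the chi-square and t-tests as descriptive, and word the registry conclusion as an adjusted association.
5. State whether the 10% target is absolute or relative.

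The cost is wording and modest analysis work, with essentially no new data as far as the article shows; the case report form itself is not available to confirm this. The unadjusted p-value loses its headline role, and adjustment cannot remove confounding by factors that were not recorded.

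### The registry plan names Student's t-test for operative time and blood loss in a cohort planned at 2:1; Welch's test keeps the 5% level whether or not the SDs are equal

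*Protocol article*

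**What the plan says.** The Statistical analyses section of the protocol article states: "The Chi-square test and Student t-test will be conducted between homogeneous cases of 2 groups in the outcome variables". It goes on to give operation-related events as examples of those variables: "operative time, hemorrhagic volume, electrophysiological changes". The first two are continuous, so the t-test is the one of the two named tests that fits them. No unequal-variance form, rank test or variance check is named for them. The section does not define homogeneous cases and does not say how many there will be in each group.

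The only registry group sizes given are in the Registry set part of the Sample size section: "800 cases will receive hybrid operations, and 400 cases will receive microsurgical operations". Under Group assignment and treatment, registry patients are allocated by clinical condition and personal wish, not at random. HO combines microsurgery with embolization or balloon occlusion; TO is microsurgery alone.

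The primary outcome (Outcome evaluation) is binary, and the Statistical analyses section assigns the Chi-square test to the trial set.

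**The concern.** Student's t-test estimates one common variance for both groups. When group sizes differ, the larger group dominates that estimate, while the true variance of the mean difference depends more on the smaller group. If the SDs also differ, the standard error settles on a wrong value. More patients do not help: a large sample deals with skewness through the central limit theorem, but it does not repair a biased standard error.

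Equal SDs cannot be taken for granted here. The two groups undergo different procedures, and they are not randomised, so case mix may differ as well. At stake are the p-values for operative time and blood loss, which the plan uses when it compares the safety and efficiency of the two operations. Depending on which group is more variable, the test would either miss real differences too often or declare differences too often.

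**Working it through.** **Inputs from the protocol article**
- Host-centre capacity: "the operative capacity of Beijing Tiantan Hospital is about 220 cases of bAVMs per year".
- Other centres: "of other participating centers is 20 cases per year in total".
- Total: "A total of 1200 cases will be recruited into the cohort in the 5-year-recruitment".
- Split: 800 HO and 400 TO.
- Significance level: 0.05 is stated for the trial set only.

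**Assumptions**
- Two-sided 5% for the registry t-tests.
- The compared cases keep the planned 2:1 split.
- SD ratio r = SD(HO)/SD(TO), varied from 0.5 to 2 because no SDs are given.

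**Step 1: reproduce the plan's own figure.** (220 + 20) × 5 = 1200, and 800 + 400 = 1200. Both agree with the stated total.

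**Step 2: pooled against true variance.** Set SD(TO) = 1 and SD(HO) = r. In large samples:
- Pooled variance: sp² = (800r² + 400)/1200 = (2r² + 1)/3
- Variance of the difference as Student's test estimates it: sp² × (1/800 + 1/400) = sp² × 3/800 = (2r² + 1)/800
- True variance of the difference: r²/800 + 1/400 = (r² + 2)/800
- Ratio of estimated to true: R² = (2r² + 1)/(r² + 2)
- True type I error: 2 × [1 − Φ(1.96 × R)]

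**Step 3: put the numbers in.** The simulation columns used 20,000 normal data sets per setting at 800 vs 400.

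| r = SD(HO)/SD(TO) | R² | R | 1.96 × R | True rate, Student (formula) | Student (simulated) | Welch (simulated) |
|---|---|---|---|---|---|---|
| 0.5 | 1.5/2.25 = 0.667 | 0.816 | 1.600 | 11.0% | 10.9% | 5.0% |
| 0.67 | 1.898/2.449 = 0.775 | 0.880 | 1.725 | 8.5% | 8.7% | 5.1% |
| 0.8 | 2.28/2.64 = 0.864 | 0.929 | 1.821 | 6.9% | 6.6% | 4.7% |
| 1 | 3/3 = 1 | 1 | 1.960 | 5.0% | 5.1% | 5.1% |
| 1.25 | 4.125/3.5625 = 1.158 | 1.076 | 2.109 | 3.5% | 3.7% | 5.3% |
| 1.5 | 5.5/4.25 = 1.294 | 1.138 | 2.230 | 2.6% | 2.9% | 5.3% |
| 2 | 9/6 = 1.5 | 1.225 | 2.400 | 1.6% | 1.6% | 5.1% |

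R is the factor by which the standard error is wrong: about 18% too small at r = 0.5 (R = 0.816) and about 22% too large at r = 2 (R = 1.225). The small gaps between formula and simulation are simulation noise; a larger repeat agreed with the formula to within 0.1 percentage points in every row.

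**Step 4: does sample size cure it?** No. R² depends on the split and the SD ratio only. At 80,000 vs 40,000 the formula gives the same rates.

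**Step 5: when does it vanish?** With n in each group, the estimated variance is [(r² + 1)/2] × (2/n) = (r² + 1)/n, which equals the true variance. So R = 1 and the rate is 5.0% at every SD ratio, both at 400 vs 400 and at 118 vs 118. The distortion needs unequal sizes and unequal SDs together.

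**Step 6: skewed data.** With log-normal data of equal means at 800 vs 400, Student's test gave 12.1% when TO was the more variable group (log-scale SDs 0.5 HO, 1.0 TO) and 1.6% when HO was. Welch's test gave 5.5% and 5.0%. Welch alone is enough for error control, without a log transformation.

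**The case against.** Several points on the other side are sound.

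- **The denominator is not stated.** A reader might infer that the t-test is fixed for 800 against 400 patients. The text does not say so: the split is a recruitment plan, and the test applies to homogeneous cases that are not defined. If those cases turn out similar in number, the distortion largely disappears. This stands, and makes the finding conditional. It does not remove it, because no matching to equal numbers is mentioned and 2:1 is the only registry split given.
- **The 11% figure is tempting but not supported as the expected result.** It needs the smaller TO group to have twice the SD of HO. The one mechanism visible in the protocol, an extra endovascular step in the larger HO group, points the other way, to rates of 2.6% or 1.6%. With no SDs given, neither size nor direction can be fixed.
- **The article may be using the name loosely.** It never says pooled or equal variance, and the form of the test could be settled in an analysis plan that is not shown. But a test is named here, and its ordinary meaning is the pooled one. The comment concerns a stated choice, not missing detail.
- **The variables are supportive.** Operative time and blood loss are examples of operation-related events. They are not the primary outcome and are not listed among the secondary outcomes of mortality, complications and residue. This stands.
- **Confounding matters more.** Registry allocation follows clinical condition, and a better variance estimate does not change that. This stands too.

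**Conclusion.** The point holds as a minor, conditional one. The plan names a test whose error rate depends on equal variances, for a cohort planned at 2:1 between groups treated differently. If the compared cases keep about that split, a nominal 5% becomes about 2.6% to 1.6% when HO is 1.5 to 2 times as variable as TO, and about 8.5% to 11% when the HO/TO ratio is 0.67 to 0.5. These figures rest on an assumed split, assumed SD ratios and a two-sided 5% level.

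The documents do not support a stronger reading, namely that the registry comparison as a whole has an inflated false-positive rate, or that the error must favour one operation. The primary outcome is unaffected because it is binary. The trial set is unaffected because it is tested by Chi-square.

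**What to change.** In the Statistical analyses section, replace Student's t-test with Welch's unequal-variance t-test for continuous outcomes, and define the homogeneous cases so that the compared numbers are known. Welch's test is valid whether the groups turn out equal or unequal in size or SD. It loses almost nothing when the SDs are equal: at r = 1 both tests rejected 5.1% of the time in simulation.

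The cost is a change of wording. The sample size stays the same, and the unequal-variance result is standard software output. A log-scale analysis is not needed for error control and changes the quantity estimated, from a difference in means to a ratio of geometric means; if wanted at all, it should be an optional sensitivity analysis. Confounding in the non-randomised comparison has to be handled separately.
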